### 3.6. Qualitative Assessment

Approximately 12 patient participants allocated to the TGs and ACG, together with their respective family caregivers, will be invited to take part in semi-structured interviews to share their perceptions on the efficacy of sessions for DFU healing. The interview guide consists of open-ended questions to be administered individually to patients and the family caregiver indicated by the patient. The script will be unchanged throughout the interviews. All interviews will be audio-recorded in digital audio and transcribed verbatim. The transcribed interviews will be anonymized to safeguard the confidentiality of data and participants.

Qualitative analysis of the interviews will be performed shortly after the transcription of the interviews. Interview contents will be inductively coded and theoretically analyzed through the thematic content analysis technique and later compared to the existing literature. To process, organize, code, and thematically analyze data, the NVivo software (QSR International PtyLtd, Melbourne, Australia) will be used. Researchers 1, 2, and 3 will be responsible for the interview implementation and the data analysis.

## 4. Interventions

### 4.1. Trial Arms

All participants will receive standard of care medical/nursing treatment for DFU, according to the guidelines of the Portuguese General Health Direction [46] and the International Working Group on the Diabetic Foot [47].

#### 4.1.1. Intervention Groups

Participants in the intervention groups are allocated in TG1 or TG2. Participants allocated to TG1 will receive four individual sessions of muscle relaxation with guided imagery (MR + GI), a technique of alternately tensing and relaxing muscle groups individually throughout the body. Relaxation intervention begins with diaphragmatic breathing, followed by Jacobson’s progressive muscle relaxation, which involves the contraction and subsequent relaxation of the 16 muscle groups of the body (hand, forearm, biceps, upper forehead, eye, nose, mouth, jaw and throat, neck, shoulder, chest, stomach, thigh, leg, and foot). The contraction will be performed for seven seconds while the relaxation lasts for about 40–50 s. The relaxation of the foot muscle group will not be performed on the foot with the wound because dressing and bandages may restrict the foot movements and, together with the typical joint stiffness of the diabetic foot, will render difficult the performance of exercise. After the muscle relaxation exercises, the guided imagery focused on the DFU healing process will initiate. The participant will be instructed to think about his/her current state of health and to imagine the DFU as a decreasing dark area and the healing process as a light associated with pleasant sensations. After being trained by the Lead Researcher, Researcher 1, 2, or 3 will be responsible for conducting the TG1 sessions in the respective hospitals.

In the TG2, participants will benefit from four individual sessions of hypnosis with guided imagery (H + GI), conducted by three qualified hypnotherapists external to the research study. The first session begins with the Eye-Roll Test for Hypnotizability [48]. Each session follows the Hypnotic Protocol with the following steps: pre-talk/absorption/ratification/alitiation/dissociation/awakening. All hypnotic sessions will train participants in the visual, auditory, and kinesthetic perception of ulcer healing, and will also promote medical treatment adherence.

The protocol for both treatment groups includes four scripted sessions, each one with duration of approximately 45 min, delivered once every two weeks, resulting in approximately a 2-month treatment course. Sessions will be conducted in a consulting room reserved by the hospital for the study, where patients will lie on a specialist couch.

#### 4.1.2. Control Groups

Participants in the ACG will receive neutral guided imagery sessions, i.e., sessions focused on the patient’s daily life before the DFU. Neutral sessions are conducted by Researchers 1, 2, and 3 following a scripted protocol that includes four biweekly sessions of approximately 45 min, each one dedicated to a different topic (family, work, friends, and leisure). Initially, the participant will be asked to choose a specific event related to the topic of the session, positive or negative, without telling the researcher which event he/she thought about. Then, the participant will answer several questions regarding the episode to promote a more detailed reconstruction of the event, being instructed to only think about the answers and not to reply orally. When the whole episode is remembered, the participant will be asked to tell what he/she imagined/remembered regarding each of the questions. The goal of the placebo sessions is to control for the effect of the received attention, from psychologists and hypnotherapists, on patients in the treatment groups. It is possible that the privileged contact may positively influence the patient’s healing process. Therefore, the attention control condition will allow us to differentiate between the impact of interventions versus the attention given to the ACG.

Participants in the PCG will not receive any intervention besides the standard of care medical/nurse treatment. Both passive and active control patients will complete the same outcome questionnaires as the participants allocated to the interventions, at the same time intervals.

### 4.2. Adherence to the Treatment Plan

Patients will be fully informed about the study goals, procedures, and potential benefits that may arise from the results of the DFU treatment. Assessment moments, intervention, and placebo sessions will be scheduled for diabetic foot appointment days so that patients will not have to go to the hospital on purpose to participate in the study. Before the appointment day, Researchers 1, 2, and 3 will call patients to remind them of their appointment with the research team for the purpose of the study. Participants will be asked to complete the last assessment (T2) even if they miss the mid-term assessment (T1).

To engage the health professional staff (e.g., physicians, nurses, podologists), meetings will be held with the physicians responsible for the multidisciplinary consultation of diabetic foot and head nurses (in the three hospitals involved in the study), in order to introduce the study and clarify any questions that may arise.

## 5. Statistical Analysis

### 5.1. Sample Size

Using Sakpal’s formula [49] and according to the descriptive results of the pilot study [50], considering the difference in the mean (1.93) and standard deviation (6) of the treatment versus passive control groups, with a statistical power of 80% and a statistical significance level of 5%, a definitive RCT will require 152 participants. Considering a dropout rate for intervention sessions of 11%, a definitive RCT with four groups will require a sample size of 169 participants, with 42 patients per group [49].

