## 2. Methods

### 2.1. Objectives

The present study aims to:Assess the effectiveness of a muscle relaxation intervention with guided imagery (TG1) compared to hypnosis with guided imagery (TG2) versus a neutral guided imagery placebo (ACG) and a group that does not receive any psychological intervention (PCG) regarding DFU healing, physiological indicators of healing prognosis, and QoL in patients with clinical distress and a chronic DFU.Understand the perspectives of patients and family caregivers on the efficacy of TG1 and TG2 interventions versus ACG sessions for DFU healing.

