### 5.2. Data Analysis

The baseline data of the treatments and control groups will be compared using the chi-squared test for binary variables and the independent sample t-test for continuous variables. To prevent overestimating the impact of both interventions, an intention-to-treat approach will be assumed to evaluate the impact on the primary and secondary outcomes. The comparison between the treatment groups versus control groups over time (differences between and within) will be performed through mixed general linear models of analysis of variance for repeated measures. Effect sizes (Cohen’s d coefficient) will also be provided between T0 and T1, T1 and T2, and T0 and T2 to determine if the intervention shows any treatment effect. A significance level of 0.05 will be set for a two-sided test, and the 95% confidence interval will be calculated. In addition, time to complete wound healing and time to favorable healing prognosis (based on the wound size) will be estimated using survival analysis, specifically, single variable and multivariable Cox proportional hazard ratio regression models and Kaplan–Meier plots. All previous analyses will include the DFU stage at the baseline as a control variable. Other confounding clinical factors associated with the outcome variables will also be considered in the statistical analysis.

The data will be analyzed using the Rstudio, R version 3.6.2 (R Core Team, Vienna, Austria) and the SPSS statistics, v. 24.0 (IBM Corp., Armonk, New York, NY, USA).

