The multicenter and randomized design of this PSY-DFU study, together with the used mixed-methods approach, is one of its major strengths. Results will answer the question, “Which psychological intervention is more effective and has more impact on the primary and secondary study outcomes in clinically stressed patients?” The findings will help to clarify the mechanistic underpinnings of the relationship between distress and chronic wound healing, the knowledge that is still very limited in general and nonexistent in DFU. The RCT is enhanced by the qualitative nested study, as qualitative data are expected to refine findings regarding the effectiveness of each intervention, allowing a better understanding of the impact of psychological factors on the DFU healing process.

Finding psychological and biological clues from specific patient groups with chronic DFUs will help health professionals tailor better treatments with precision that could prevent future diabetic foot wounds from developing or from recurring. Specifically, identifying the specific risk profile of patients will best provide health professionals with important information regarding their psychological vulnerabilities, which may make it difficult for DFU healing. Additionally, survival analysis will help to identify the best assessment moments to initiate psychological interventions to contribute to the DFU healing, and prevent the onset of new wounds. Therefore, this study is of important clinical relevance regarding DFU healing and recurrence, as well as QoL, and may also contribute to the decrease in health care and medical-related costs associated with DFU treatments, including amputations.

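### The 80% power in 5.1 comes from treatment versus passive control alone and, at 42 per group, holds for no pairwise contrast, including the active-control and head-to-head comparisons that the protocol promises to answer

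*Protocol article*

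**What the plan says.** Section 5.1 (Sample Size) holds the only sizing statement. Its sole input is a pilot result, "considering the difference in the mean (1.93) and standard deviation (6) of the treatment versus passive control groups". With 80% power and a 5% level it concludes that "a definitive RCT will require 152 participants". It then allows for 11% dropout and arrives at 169 patients in four groups, 42 per group. Section 5.2 sets the test: "A significance level of 0.05 will be set for a two-sided test".

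The comparisons the trial undertakes to make are wider than the one it sized:

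- **Treatment versus ACG.** Primary aim (i), under 2.1, compares both treatment groups with the control groups, in the plural. Section 2.2 describes the trial as sham-controlled. Section 4.1.2 says that "the attention control condition will allow us to differentiate between the impact of interventions versus the attention given to the ACG".
- **TG1 versus TG2.** The first objective in 2.1 sets relaxation against hypnosis as well as against both controls. Section 7 states that the results will settle the question "Which psychological intervention is more effective and has more impact on the primary and secondary study outcomes in clinically stressed patients".

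Section 5.1 gives no effect size or power for either of these. It also does not name the outcome on which 1.93 and 6 were measured, although 3.3 lists several primary outcomes.

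**The concern.** A power statement belongs to a contrast and an effect size. The difference between a treatment and no psychological intervention is not the natural planning value for treatment versus attention control. Section 4.1.2 itself allows that contact with the psychologist or hypnotherapist may help healing; if it does, the difference from ACG is smaller than the difference from PCG. Nor is it the natural value for two interventions that share guided imagery, number of sessions, session length and schedule (4.1.1).

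The stake is how a null result is interpreted. If these contrasts have little power, a non-significant TG1–TG2 or TG–ACG difference says little. Yet the Discussion announces an answer to which intervention is better, and 4.1.2 announces that technique and attention will be told apart. A reader who trusts the printed 80% could take a null result as equal effectiveness, or as evidence that only attention mattered.

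**Working it through.** **Inputs.** Difference 1.93, SD 6, power 80%, level 5%, total 152, dropout 11%, 169 in total, 42 per group (all from 5.1); two-sided test (5.2); four equal groups (2.4). Evaluable patients per arm: 152/4 = 38.

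**1. Reproducing the plan's figure.** The two-group formula for means is n per arm = 2(z₀.₉₇₅ + z₀.₈₀)²σ²/δ².

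2 × (1.96 + 0.8416)² × 36 / 1.93² = 151.7, so 152.

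The printed 152 is therefore the number *per arm* for one two-group comparison, but 5.1 uses it as the total for four arms. The inflation also reproduces: 152 × 1.11 = 168.7, so 169, and 169/4 = 42.25.

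**2. Power for the full 1.93 at the planned size** (noncentral t, SD 6, two-sided 5%):

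| Comparison | Power |
|---|---|
| 38 vs 38 (any pair of arms, TG vs PCG included) | 28% |
| 42 vs 42 (no dropout) | 31% |
| 76 vs 38 (both treatments pooled vs PCG) | 36% |
| 76 vs 76 (both treatments vs both controls) | 50% |
| 152 vs 152 | 80% |

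**3. Precision of a pairwise contrast at 38 per arm.**

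- Standard error: 6 × √(2/38) = 1.38.
- Difference detectable with 80% power: 2.80 × 1.38 = 3.86. This is twice 1.93, as it must be, because 38 is a quarter of 152.
- 95% CI half-width: 1.96 × 1.38 = 2.70, so the full width is about 5.4.

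The band from −1.93 to +1.93 is 3.86 wide. An interval 5.4 wide can never lie wholly inside it. At this SD and size, no result could therefore confine a TG1–TG2 difference to less than the planning effect in both directions.

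**4. Smaller differences.** The documents give no figure for TG–ACG or TG1–TG2. Taking 25%, 50% or 75% of 1.93 as an assumed range:

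| Share of 1.93 | Difference | Power, 38 per arm | Power, 152 per arm |
|---|---|---|---|
| 25% | 0.48 | 6% | 11% |
| 50% | 0.97 | 11% | 29% |
| 75% | 1.45 | 18% | 55% |

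The last column separates this point from the per-arm/total confusion in step 1: putting 152 patients in every arm would restore 80% for a difference of 1.93 but not for differences in this range.

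**5. Could the analysis model close the gap?** For 80% power at 1.93 with 38 per arm, the SD would have to be 1.93 × √(38/2) / 2.80 = 3.0, half the stated value. Section 5.1 claims no such reduction.

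**The case against.** Several counter-arguments deserve weight.

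- *Sizing a multi-arm trial on one contrast is common, and 5.1 names the contrast it used.* True, and the absence of separate calculations would not be a fault by itself in a condensed article. The fault is that the text attaches 80% to a four-group trial of 169, where it holds for no pair of arms, while promising answers on contrasts that were never sized.
- *TG1 versus TG2 is not a listed primary aim.* This stands. Aim (i) sets the treatments against the controls, aim (iii) is qualitative and against ACG, and 5.2 describes treatment versus control groups. The head-to-head claim rests on the first objective in 2.1 and the sentence in section 7. The TG–ACG contrast is better anchored.
- *The 25% to 75% range is assumed.* It is. Section 4.1.2 says only that attention may help, and that TG1 and TG2 differ by less than either differs from PCG is inference. The central figure does not need the range: even the full 1.93 has about 28% power.
- *Baseline adjustment and repeated measures (5.2) will improve precision.* Probably, by an unstated amount; step 5 shows how much would be needed.
- *Section 5.2 already commits to confidence intervals and effect sizes.* It does, which makes the remedy easy. No section says that a non-significant result will be read as equality or as no effect beyond attention. A reader might infer that from the Discussion, but the documents do not state it.

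Two other inferences are tempting and should be resisted. One is that 80% at least holds for treatment versus PCG; at 38 per arm it does not. The other is that the interval could exclude a difference beyond 1.93 in a given direction only with an extreme estimate. In fact an estimate more than 2.70 − 1.93 = 0.77 to the opposite side does so. That is 0.56 standard errors, and an estimate at least that far from zero, on one side or the other, occurs in about 58% of trials when the true difference is zero. What cannot happen is exclusion in both directions at once.

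**Conclusion.** The point holds. The 80% in 5.1 was derived for one contrast, treatment versus PCG, and at 42 per group it is delivered for no pairwise contrast. Power is about 28% for a difference of 1.93 (31% without dropout), the detectable difference is about 3.9, and the 95% CI half-width is about 2.7. No effect size or power supports treatment versus ACG, which is part of the primary aim, or TG1 versus TG2, which the Objectives and Discussion promise.

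These figures assume SD 6, a two-sided 5% level, 38 evaluable per arm and no gain from covariates, and they are on the unnamed scale of the pilot outcome. The 6% to 18% power (11% to 55% at 152 per arm) for smaller differences depends further on the assumed fractions. The documents do not show that a null result will be misread; they leave the reader with a power figure and a promise that invite it.

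**What to change.** **Section 5.1.** State that the calculation concerned treatment versus PCG only and name the outcome behind 1.93 and 6. Do not leave 80% standing for any contrast at 42 per group. Add, for example: *With 38 evaluable patients per group and SD 6, a pairwise difference of 1.93 has about 28% power; the difference detectable with 80% power is about 3.9 and the 95% confidence interval half-width about 2.7, before any gain from baseline adjustment. No effect size was assumed for treatment versus ACG or for TG1 versus TG2.* Correct the use of 152 as a four-arm total in the same edit, since the per-arm figures depend on it.

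**Section 7.** Replace the sentence saying that the results will answer which intervention is more effective with, for example: *Differences between TG1 and TG2, and between each treatment and ACG, will be estimated with 95% confidence intervals. A non-significant difference will not be interpreted as equal effectiveness or as absence of an effect beyond attention.*

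**Cost.** Wording in two places and a less favourable stated power. No change to enrolment, conduct or data collection, and no additional patients. For reference, 80% power for a difference of 1.93 in each pairwise contrast, without multiplicity adjustment, would take 4 × 152 = 608 evaluable patients.

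### 152 is the number the formula gives for each group, but the plan uses it as the total for four groups; power for one arm against passive control is about 28–31%, not 80%

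*Protocol article*

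**What the plan says.** Section 5.1 sizes the trial on a two-group contrast from the pilot study, "considering the difference in the mean (1.93) and standard deviation (6) of the treatment versus passive control groups". From these values the section concludes that, "with a statistical power of 80% and a statistical significance level of 5%, a definitive RCT will require 152 participants". After an 11% allowance for dropout from sessions, it states that "a definitive RCT with four groups will require a sample size of 169 participants, with 42 patients per group".

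The abstract confirms that about 170 patients is the size of the whole trial, and section 2.4 allocates them equally to TG1, TG2, ACG and PCG. Section 5.2 settles the sidedness: "A significance level of 0.05 will be set for a two-sided test". The discussion also undertakes to settle a head-to-head comparison of the two treatment arms, which it words as follows: "Which psychological intervention is more effective and has more impact on the primary and secondary study outcomes in clinically stressed patients".

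**The concern.** A standard two-mean calculation returns the number needed in each group. Section 5.1 treats its result as the number for the whole trial and then divides it by four. If 152 is the per-group figure, each arm has a quarter of the patients that the plan's own inputs require, and the 80% power stated in the article does not exist for any comparison of two arms.

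This matters for interpretation. A reader who is told that power was 80% may take a non-significant result as evidence against relaxation or hypnosis, when the trial had less than a one-in-three chance of detecting the effect it was planned on. The planning difference is also against passive control. Section 4.1.2 says that attention alone may help healing, so differences from the active control could be smaller than 1.93. The same may be true of the difference between TG1 and TG2. The article gives no figure for either contrast.

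**Working it through.** **Inputs.** Difference δ = 1.93, SD σ = 6, power 80% (z = 0.842) and dropout 11%, all from section 5.1. Two-sided 5% (z = 1.960) from section 5.2. Four equal arms from section 2.4. The standardised difference is 1.93/6 = 0.322.

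**Reproducing the plan's figure.**

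n per group = 2 × (z₀.₉₇₅ + z₀.₈₀)² × σ² / δ² = 2 × (1.960 + 0.842)² × 36 / 1.93² = 151.7, rounded up to 152.

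The t-distribution version gives 152.7. The stated 152 is therefore reproduced, but as a per-group number.

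**Could 152 be a total under some other reading?** None of those tried gives it:
- two-sided, 1:1: total 304
- one-sided, 1:1: 120 per group, total 240
- two-sided, 2:1 allocation: total 342
- two-sided, 90% power: 204 per group, total 408

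**The plan's next steps.** 152 × 1.11 = 168.7, stated as 169. 169/4 = 42.25, stated as 42. Before the dropout allowance, 152/4 = 38 per arm.

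**Power at the planned size.** Power ≈ Φ(δ / (σ√(2/n)) − 1.960).
- n = 38: standard error 6 × √(2/38) = 1.376; 1.93/1.376 = 1.402; Φ(1.402 − 1.960) = Φ(−0.558) = 29%.
- n = 42: standard error 6 × √(2/42) = 1.309; 1.93/1.309 = 1.474; Φ(1.474 − 1.960) = Φ(−0.486) = 31%.

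Exact t-test power, two-sided 5%, for a difference of 1.93:

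| Comparison | 38 per arm | 42 per arm |
|---|---|---|
| One arm v one arm | 28.3% | 30.8% |
| TG1 + TG2 v PCG (76 v 38; 84 v 42) | 36% | 39% |
| TG1 + TG2 v ACG + PCG (76 v 76; 84 v 84) | 50% | 54% |

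With 152 v 152 the t-test power is 79.8%, which confirms the per-group reading. Even a one-sided test at 38 per arm reaches only 40%.

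**Difference detectable with 80% power.** (1.960 + 0.842) × 1.376 = 3.86 points at 38 per arm, and 2.802 × 1.309 = 3.67 at 42. The t-based values are 3.91 and 3.71. At 38 per arm this is 3.91/6 = 0.65 SD, and 3.91/1.93 = 2.0 times the planning difference.

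**Size that the inputs would require.** 2 × 152 = 304 evaluable patients for one comparison and 4 × 152 = 608 for four arms. With 11% loss, 152/0.89 = 170.8, so 171 per group and 4 × 171 = 684 in all.

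**Dropout step.** Allowing for 11% loss means dividing by 0.89, which turns 152 into 171. Multiplying by 1.11 gives 169, which leaves 169 × 0.89 = 150 after the loss.

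**The case against.** Nobody who repeats the formula can dispute that 152 is per group. The strongest case on the other side is that 28% is the lowest of several defensible figures.

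- **Evaluable patients.** The 11% is a dropout rate from sessions. The analysis is by intention to treat, and section 4.2 asks patients to attend T2 even if they miss T1, so patients who leave the sessions may still be assessed. That supports 42 per arm and 31%. This stands, and a range of 28–31% is the fair statement.
- **Pooling.** The aims and section 5.2 can be read as treatment arms together against control arms together, which gives 50–54%. This too stands as a reading, but it is still far from 80%, and the planning difference was taken against passive control only.
- **Adjustment.** Section 5.2 plans repeated-measures models that control for baseline ulcer stage. The article gives no baseline–outcome correlation. Assuming that SD 6 is a raw-score SD, that variance falls by the factor 1 − ρ², and that ρ is 0.5 to 0.7, power at 38 per arm would be about 36–49%, and 62–79% for 76 v 76. Reaching 80% at 38 per arm needs ρ of about 0.87. If SD 6 already describes change scores, the gain may not apply.

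Three smaller objections are fair. The dropout slip is two patients and changes nothing that matters. The outcome behind 1.93 and 6 may be named in the pilot report or the full protocol. Section 5.1 claims power only against passive control, so there is no explicit power claim for TG1 v TG2 or for treatment v ACG to withdraw. What remains there is a promise in the discussion with no stated power behind it.

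**Conclusion.** The concern holds. A per-group requirement was used as the total for four arms, so each arm has a quarter of the patients that the plan's inputs call for, and the stated 80% power is wrong. For one treatment arm against passive control, power is 28% with 38 evaluable patients per arm and 31% with 42. This assumes the stated difference and SD, a two-sided 5% level and no covariate adjustment. The pooled readings give 36–54%. Adjustment could raise these figures, but only through a correlation that the article neither states nor uses.

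This must be corrected, because the power statement is the stated basis for the trial's size and will shape how a null result is read. The dropout arithmetic and the unnamed outcome are minor points to put right in the same paragraph.

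**What to change.** Rewrite section 5.1 without changing enrolment:

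- State that 152 is the number required per group for a difference of 1.93 with SD 6.
- State that 38–42 patients per arm give about 28–31% power for that difference, and 80% power only for about 3.7–3.9 points. If a pooled treatment-versus-control comparison is intended, say so and give its 50–54%.
- If the adjusted model is to be relied on for more power, state the assumed correlation, its source and the resulting figure.
- Name the outcome and time point to which 1.93 and 6 belong.
- Correct the dropout step to division by 0.89.
- Say that no power was calculated for TG1 v TG2 or for treatment v ACG. Report these contrasts as estimates with the 95% confidence intervals already planned in section 5.2, and soften the discussion's promise to show which intervention is more effective.

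The cost is rewording section 5.1 and the conclusions that lean on it, and a less favourable power statement. No extra patients are needed. Keeping the 80% claim for a single pairwise comparison would instead take about 304 evaluable patients in two arms, or 608 in four.
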